#### Secondary Outcomes

The secondary outcomes include examining neuropathy score, ABI, and random blood glucose. The neuropathy score will be assessed following a previous study [23], using a 10-g Semmes-Weinstein Monofilament. During the monofilament testing, the participants will be instructed to lie flat on the examination table. To ensure that they could not see their feet, a standard monofilament (5.07/10-gram Semmes-Weinstein nylon monofilament) will be used to lightly apply pressure to three specific areas of the participants’ feet: (1) the underside of the first metatarsal head, (2) the underside of the fifth metatarsal head, and (3) the top surface between the first and second metatarsals. The monofilament will be positioned on the foot’s surface, forming a perpendicular angle with the skin. The pressure will be gradually intensified until the filament is bent, indicating the application of a predetermined level of pressure. The sites will be examined in a random order, rather than following a specific sequence. If the examinee provided the correct response at any site during the test, further testing at that site was not necessary. However, if the examinee could not correctly identify the interval in which the stimulus was applied, the test would be repeated at that site up to 2 times, aiming to obtain 2 similar correct responses. A site will be considered sensate if either the first response is correct or 2 out of 3 tests yield a correct response. On the other hand, a site will be classified as insensate if there are 2 incorrect responses and 2 “unable to determine” responses or 1 incorrect response and 1 “unable to determine” response. The presence of an insensate area at any of the 3 sites indicates a positive result for peripheral neuropathy in the monofilament test [24,25].

The ABI will be determined by measuring the systolic blood pressure in the arm and leg after a 10-minute rest in a supine position, with both arms and legs straight and relaxed [26]. Manual cuffs will be used for all blood pressure measurements, and the appropriate cuff size will be selected based on the arm circumference determined during screening. The same cuff size will be used for the lower leg, and a straight wrapping technique will be employed. The arm blood pressure will be measured using a sphygmomanometer along with an 8 MHz Doppler device to detect pulses. A single measurement will be taken at each of the 6 sites in the following sequence: left arm, left ankle (dorsalis pedis and posterior tibialis), right arm, and right ankle. The right ABI will be calculated by dividing the higher-pressure measurement from the right ankle (dorsalis pedis or posterior tibialis) by the higher brachial pressure (right or left side). The left ABI will be calculated using a similar method. The lower ratio from either side will be considered as the participant’s ABI [27].

To evaluate the random blood glucose levels, blood samples will be obtained from the capillary of the index finger for each patient. Subsequently, the Accu-Chek Active glucometer, a device manufactured in Germany, will be used to measure the samples, and the recorded values will be documented [28].

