### Statistical Analyses

The demographic characteristics of all participants will be summarized using descriptive statistics, such as means (SDs), frequencies, and ranges, which will be presented in a tabular form. Statistical analysis of the data will be performed using the SPSS statistical software (version 2, SPSS Inc). *P*<.05 will be considered statistically significant. The normality of the data will be assessed using the Kolmogorov-Smirnov test. Numerical variables will be presented as mean (SD) or median (IQR) values, while categorical variables will be presented as frequency (percentages). To determine differences in numerical variables between the therapeutic cookies and placebo groups, independent sample *t* tests or Mann-Whitney *U* tests will be used. The same tests will also be used to compare alterations in outcome variables between the 2 groups. For within-group comparisons, paired-sample *t* tests or the nonparametric Wilcoxon test will be used. To account for the effects of confounding factors, a general linear model will be applied. In addition, analysis of covariance will be used to account for the effects of confounding factors when appropriate.

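### The first criterion for an insensate monofilament site needs four responses where at most three are taken, so sites with only incorrect or only undetermined answers have no classification

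*Protocol article*

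**What the plan says.** All of the scoring text is in the protocol article, Methods, Secondary Outcomes. After a first response that is not correct, "the test would be repeated at that site up to 2 times, aiming to obtain 2 similar correct responses". The sensate rule confirms the ceiling of three: "A site will be considered sensate if either the first response is correct or 2 out of 3 tests yield a correct response".

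The insensate rule has two branches. Under the first, "a site will be classified as insensate if there are 2 incorrect responses and 2" 'unable to determine' responses. The second is "1 incorrect response and 1" 'unable to determine' response. No default is given for a site that meets neither definition.

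Site results are combined by a single rule: "The presence of an insensate area at any of the 3 sites indicates a positive result" for peripheral neuropathy.

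The Outcomes section lists the neuropathy score as a secondary outcome. Table 1 schedules it at Week 2 and Week 5, that is, before and after supplementation. Statistical Analyses introduces the t test and the Mann-Whitney test with "To determine differences in numerical variables between the therapeutic cookies and placebo groups", and then applies the same tests to changes in the outcome variables.

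**The concern.** A scoring rule must place every obtainable result in exactly one category. Here one of the two insensate branches is unreachable, and the branch that remains demands a mixture of incorrect and undetermined answers. The rule therefore says nothing about a site where the participant is wrong every time or can never tell. Yet it calls a site insensate when one of the three answers was correct and the other two were one incorrect and one undetermined.

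The gap reaches the participant's result because a single insensate site decides it. If an unclassified site is counted as not insensate, and neither of the other two sites is insensate, the participant is recorded as negative. If it is left open, the result is undetermined. The examination is done twice, so filling the gap one way at the first visit and another way at the second would show as a change in neuropathy status that the rule itself produced.

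A second, smaller matter is the link between name and analysis. The outcome is called a score, but the only result this section defines is positive or negative.

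**Working it through.** **Inputs, all from Secondary Outcomes**

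- Tests per site: one first test plus at most two repeats.
- Sensate: first response correct, or two of three correct.
- Insensate, branch 1: two incorrect and two undetermined.
- Insensate, branch 2: one incorrect and one undetermined.

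**Step 1: the ceiling.** 1 + 2 = 3 responses, which agrees with the two-out-of-three wording of the sensate rule. Branch 1 needs 2 + 2 = 4. Since 4 > 3, it cannot occur.

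**Step 2: the possible patterns.** Write C for correct, I for incorrect and U for undetermined. A first C makes the site sensate and ends testing. Otherwise the first response is I or U and, if both repeats are used, each can be C, I or U. That gives 2 × 3 × 3 = 18 patterns after a first miss, or 19 with the single pattern C.

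**Step 3: classify the 18 patterns**

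| Reading of the insensate counts | Sensate | Insensate | Neither | Total |
|---|---|---|---|---|
| At least one I and at least one U | 2 | 10 | 6 | 18 |
| Exactly one I and exactly one U | 2 | 4 | 12 | 18 |
| First 'and' read as 'or', counts as at least | 2 | 16 | 0 | 18 |

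- Sensate in every row: ICC, UCC.
- Neither, on the 'at least' reading: III, IIC, ICI, UUU, UUC, UCU.
- Neither, on the exact reading: those six plus IIU, IUI, IUU, UII, UIU, UUI.
- Insensate on the exact reading: ICU, IUC, UCI, UIC, each of which contains a correct response.

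Branch 1 is met by none of the 18. III and UUU are unclassified on both readings of the rule as printed.

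**Step 4: dependence on always taking three tests.** The text allows up to two repeats, so testing might stop once one I and one U have been seen. IU and UI then end at two responses. The patterns after a first miss number 2 × (1 + 3 + 3) = 14, and on the 'at least' reading the same six remain unclassified. The list of gaps is unchanged; only the denominator moves.

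**Step 5: a complete alternative.** Keep the printed sensate rule and call every other site insensate. After a first miss, two of three correct means that both repeats are correct, so 2 patterns are sensate and 18 − 2 = 16 insensate. This is the third row of the table: no gap and no overlap.

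**The case against.** The strongest reply is that this is a one-word slip. Reading the first 'and' as 'or' repairs the rule completely, and the text contrasts only two states, so a sensible examiner would call a site with three wrong answers insensate. That is plausible, but nothing in the article makes the correction, and treating all non-sensate sites as insensate is an inference. The article sets out the scoring steps in full here, so this is a rule stated wrongly, not detail left out for brevity.

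Other parts of the reply do stand, and they limit the point:

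- **A reader might infer that the outcome cannot be scored at all.** It can be for many sites. The sensate rule is workable and the second insensate branch is attainable.
- **A reader might see a further conflict in the stopping sentence**, "If the examinee provided the correct response at any site during the test, further testing at that site was not necessary". The next sentence begins with a contrast and deals with a participant who could not answer correctly, and the sensate rule speaks of the first response being correct. Together they limit the stopping sentence to a correct first response.
- **A reader might conclude that neuropathy will be under-detected.** That follows only if unclassified sites are counted as not insensate, which the article does not say.
- **A reader might conclude that a yes/no result will be compared by t test, with loss of information.** Statistical Analyses never says so. It introduces these tests for numerical variables, and the score is said to follow a cited study that is not shown. What stands is that the article does not connect the word 'score' to the positive/negative result.

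**Conclusion.** The insensate rule is wrong as written. Its first branch is impossible under the section's own three-test limit, and the remaining branch leaves 6 of 18 patterns after a first miss unclassified, or 12 of 18 on the exact reading. Those counts assume that both repeats are always taken after a first miss. The finding for III and UUU depends on neither choice of reading.

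The counts describe possible patterns. The article gives no response frequencies, so they must not be read as a share of sites or participants. A participant's result is at risk only when an unclassified site occurs and no other site is insensate.

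One secondary outcome is affected. The MMP-9 primary outcome and the sample size are not.

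**What to change.** - **Reconcile the insensate sentence** with the three-test limit and with the method the article cites, so that sensate and insensate together cover every pattern without overlap. One wording that does this keeps the article's own sensate rule and defines every other site as insensate. The authors should confirm it against their source.
- **Apply one rule at both visits**, fixed before the arms are compared.
- **State what the neuropathy score is.** If it is the positive/negative result, analyse it with a method for categorical outcomes and not with the tests introduced for numerical variables. If it is something else, define it.

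The cost is wording in the outcome definition and on the case-report form; the rule itself calls for no extra examination. The Results section says recruitment and testing started in January 2024, so some sites may already have been scored. If the individual responses were recorded, they can be re-scored under the corrected rule. If only the site result was kept, the authors should say how unclassified patterns were handled.

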### Outcomes

The main focus of this study, or the primary outcome, is determining the level of MMP-9. The secondary outcomes include examining neuropathy scores and ankle-brachial index (ABI) as well as assessing random blood glucose.

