### Intervention

A total of 60 eligible participants diagnosed with type 2 diabetes will be assigned randomly to either the therapeutic cookies group (n=30) or the placebo group (n=30). Over 14 weeks, participants in the intervention group will take therapeutic cookies (20 g) twice daily, while participants in the control group will take identical placebo cookies. The therapeutic cookies will be provided by Evelyn Food Supplement company, chosen for their reputation for providing high-quality, standardized ingredients, which is essential for the integrity of the study. Both therapeutic and placebo cookies will be indistinguishable in terms of weight, size, shape, taste, color, and odor. The placebo cookies are also produced by Evelyn Food Supplement company. The choice of company was made to maintain the highest research standards and to ensure that there are no conflicts of interest, financial support, or other compensation for the researchers.

The trial will consist of 3 study visits: before the intervention, 1 week after the intervention, and at the end of the intervention period. Study participants will receive instructions on how to use their supplements and will be followed up with phone calls every 3 days throughout the study. Compliance will be assessed by evaluating the number of unused supplements returned by each individual, with the remaining cookies counted to determine total supplement intake. Additionally, participants will be asked to maintain a reporting diary to document any adverse events experienced following the consumption of therapeutic cookies. If any adverse events are attributed to the consumption of therapeutic cookies, participants will be instructed to discontinue taking the supplements and will be promptly referred to a specialist for appropriate treatment. The study participants will not receive any specific dietary recommendations or dietary regimens.

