### Blood Sample Collection

Blood samples for the identification of MMP-9 will be collected from each participant at a specific time point in the morning, following an overnight fast. The samples will be drawn at approximately 8 AM to ensure consistency and minimize potential variations in MMP-9 levels due to diurnal rhythms. This fasting state collection will aim to provide a baseline measurement of MMP-9 levels. Additionally, blood samples will be collected both before and after the intervention involving the administration of cookies to assess potential changes in MMP-9 levels in response to the intervention.

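### The only glycaemic outcome is a random fingerstick with no fixed sampling condition, although participants already attend fasting at about 8 AM before and after the intervention: either the label is wrong or avoidable variance enters

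*Protocol article*

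**What the plan says.** The Outcomes section makes glucose a secondary outcome: "The secondary outcomes include examining neuropathy scores and ankle-brachial index (ABI) as well as assessing random blood glucose". The Secondary Outcomes section gives the method: "To evaluate the random blood glucose levels, blood samples will be obtained from the capillary of the index finger for each patient", read on a glucometer. Finger and device are specified. Time of day, fasting state and interval since food are not. The Abstract and Table 1 also call the outcome random.

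Table 1 places the reading in weeks 2 and 5, and supplementation in weeks 3 and 4. On diet, the Intervention section says: "The study participants will not receive any specific dietary recommendations or dietary regimens".

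The Blood Sample Collection section handles the primary outcome differently. Those samples "will be collected from each participant at a specific time point in the morning, following an overnight fast", and the reason is given: "The samples will be drawn at approximately 8 AM to ensure consistency and minimize potential variations in MMP-9 levels due to diurnal rhythms". It adds that "blood samples will be collected both before and after the intervention involving the administration of cookies". The same standardisation is not extended to glucose, and no reason is given for choosing a random value. MMP-9 has no row in Table 1, so the table does not show whether the fingerstick and the fasting draw share an attendance.

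**The concern.** Glucose lowering is a main part of the rationale in the Abstract, Introduction and Discussion, and this is the only outcome that measures it. A random value depends on when and what the person last ate. With a free diet and no fixed sampling time, that dependence enters at baseline and at follow-up, and so enters the change that the Statistical Analyses section compares between groups.

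A standardised condition is already available, since every participant gives a fasting morning sample before and after the intervention. Two things are at stake. One is interpretation: a reader cannot tell whether the reported figure is a fasting value. The other is precision: a real effect on glucose could be missed because of variation that the existing schedule could remove.

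**Working it through.** **1. The two possible readings.** The text leaves open when the fingerstick is taken.
- *At the 8 AM attendance.* The participant has fasted overnight, so the value is a fasting capillary glucose. No variance is added, but the name is wrong wherever it appears.
- *At another time.* Nothing in the protocol limits the interval since the last meal, so meal-timing variance enters at both time points.

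Either way the Blood Sample Collection and Secondary Outcomes sections need to be reconciled.

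**2. The plan's own figure.** The only sample-size figure is for MMP-9: SD 2.7 in both arms, difference 2.5, two-sided 5%, power 90%. By the normal approximation, n = 2 × (1.960 + 1.282)² × 2.7² / 2.5² = 24.5, so 25 per group, as stated. (The exact *t* calculation gives 25.5, so 26.) Nothing comparable is given for glucose, so what follows is illustrative.

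**3. Detectable difference in mmol/L.** Inputs:
- 24 evaluable per arm, which is the planned 30 less the stated attrition of about 20% (30 × 0.8).
- Two-sided 5% and 80% power (the power is assumed here).
- Within-person day-to-day fasting SD *f* = 1.0 to 1.5 mmol/L (assumed).
- Added meal-timing SD *g* = 1.5 to 4 mmol/L, independent between the two visits (assumed).

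SD(change) = √[2(f² + g²)]. Detectable difference = (2.013 + 0.850) × √(2/24) × SD(change) = 0.826 × SD(change).

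| f | g = 0 (fasting) | g = 1.5 | g = 4 |
|---|---|---|---|
| 1.0 | 0.826 × 1.414 = 1.17 | 0.826 × 2.550 = 2.11 | 0.826 × 5.831 = 4.82 |
| 1.5 | 0.826 × 2.121 = 1.75 | 0.826 × 3.000 = 2.48 | 0.826 × 6.042 = 4.99 |

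The ratio of random to fasting runs from 2.48/1.75 = 1.4 to 4.82/1.17 = 4.1.

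**4. A scale-free version.** Let *r* be the meal-timing SD divided by the SD of the fasting change, both on the change scale. The variance, and hence the required sample size, is multiplied by 1 + r². Take 25 per group and, as an assumption, the standardised effect used for MMP-9 (2.5/2.7 = 0.93). Power by the normal approximation:

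| r | Sample size × | Power |
|---|---|---|
| 0 | 1.00 | 90.6% |
| 0.25 | 1.06 | 88.8% |
| 0.5 | 1.25 | 83.3% |
| 1.0 | 2.00 | 63.9% |
| 1.5 | 3.25 | 44.3% |

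Under the model in step 3, r = g/f, so the mmol/L ranges correspond to r from 1.5/1.5 = 1 to 4/1.0 = 4. The scale-free table shows that if meal timing adds little, the loss is small.

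**The case against.** The strongest objection is that the protocol does not establish that any noise is added. If the stick is taken at the fasting draw, only the name needs correcting. That stands, and it is why the point is put as two alternatives.

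The magnitude is also open to challenge. Every glucose SD above is assumed. If a participant attends both times at a similar hour and interval after eating, with correlation ρ between the two meal-timing errors, g² becomes g²(1 − ρ) in the change score and part of the noise cancels. Real differences between people in their response, left out of the formula, would narrow the ratio further. The 5.0 mmol/L figure is therefore a worst case.

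Three stronger readings are tempting but not supported:
- *The result could reflect the acute effect of a study cookie, or a carbohydrate difference between the cookies.* Table 1 puts both readings outside the supplementation weeks. The Intervention section's different duration and its end-of-intervention visit make the timing less clear, but nothing shows that a cookie is eaten close to a reading. What replaces the two extracts in the control is not stated, and the cookies are said to match in weight and size.
- *The comparison is biased.* With random allocation and blinding, meal timing should be unrelated to arm. The loss is of precision, on one secondary outcome. MMP-9 already has fasting control.
- *A random value has no merit.* The rationale includes insulin stimulation and a lower glycaemic index, which are not purely fasting effects. The protocol gives no reason for its choice, which is not the same as there being none. A random value with meal time unrecorded would still be hard to interpret as a post-meal measure.

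**Conclusion.** The point holds as a measurement that is not pinned down. The protocol names a random glucose, fixes no sampling condition, and has participants attend fasting before and after the intervention without saying whether the two coincide. One reading gives a mislabelled outcome, the other an avoidable loss of precision.

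The direction of the second is certain under independent errors, because added variance can only raise the SD of the change. Its size is not known from the protocol: illustratively, a detectable difference of 2.1 to 5.0 instead of 1.2 to 1.8 mmol/L. It should be corrected because the correction is cheap and this is the only glycaemic outcome, but it does not threaten the primary analysis.

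**What to change.** - Take the capillary reading at the existing 8 AM fasting draw, before and after the intervention, and say so in the Secondary Outcomes section. Add the MMP-9 draw to Table 1 so that the shared attendance is visible.
- Rename the outcome *fasting capillary glucose* in the Abstract, Table 1, the Outcomes section, both places in the Secondary Outcomes section, and the registry entry.
- Analyse follow-up glucose with its own baseline as a covariate. Analysis of covariance is already among the planned methods.
- If readings have in fact been taken at the fasting draw, only the label changes.

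The cost is a dated change to one secondary outcome, with the same device and no extra visit or venous sample. The main risk lies in the transition, since the article reports that recruitment and testing began in January 2024. Participants whose baseline was not fasting should be flagged and not paired with a fasting follow-up as if the two were comparable. Report them separately, or under the condition in which both readings were taken. Time since food reconstructed afterwards from memory is a weak substitute and should be described as such.
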